#### Lipid panel

Total cholesterol, low-density lipoprotein (LDL), high-density lipoprotein (HDL) and triglycerides will be drawn and run by experienced laboratory personnel at either Rex Healthcare or WakeMed. Lipids will be determined by automated methods using the Hitachi 704 Analyzer (Roche Diagnostics). Desirable total cholesterol levels are below 200 mg/dL in adults. Normal fasting triglyceride levels are below 150 mg/dL. Desirable LDL levels are below 130 mg/dL. A low HDL is considered to be a value below 35 mg/dL, and high HDL, ≥60 mg/dL [61].

#### Blood pressure

Blood pressure will be measured with a Welch Alyn VSM 300 automatic blood pressure machine (Welch Alyn). The cuff bladder will cover at least two-thirds of the upper right arm and at least half of the circumference. The participant will sit quietly for 10 minutes prior to measurement. Blood pressure will be taken twice with at least 5 minutes between measurements, using recommended procedures [62,63].

### Weight status outcomes

Height will be measured twice and averaged on all women in street clothes without shoes. A portable stadiometer will be calibrated to 1/8-centimeter intervals. Weight will be measured twice and averaged in a private room on all women in street clothes and without shoes using a Tanita WB-110A Digital Scale. Body mass index (BMI) of mothers will be calculated twice by entering height and weight (kg/m^2^) [64,65]. In adults, overweight will be defined as a BMI between 25.0 to 29.9 kg/m^2^ and obesity will be defined as above 30.0 kg/m^2^[64,65].

### Adiposity outcomes

All adiposity measures will be taken in a private room by two research assistants. All adiposity measurements will be taken three times and averaged according to the National Health and Nutrition Examination Survey procedures [64,65]. Waist circumference will be measured using a Figure Finder measuring tape with lock (Novel Products Inc., Rockton, IL). Triceps and subscapular skinfolds will be measured using Lange skinfold calipers.

### Health behavior outcomes

The Adult Health Behavior Survey [66] will be used to collect information on intake of fruits, vegetables, sugared beverages, water, and fast food. Responses on the 23-item questionnaire will be recorded a 1 for a healthy behavior and 2 for an unhealthy behavior. Alpha coefficients in adults have ranged from 0.80 to 0.86 [66].

The Health Promoting Lifestyle Profile II (HPLP II) will be used to measure health promoting behaviors [67]. The HPLP II is a 48-item questionnaire that uses a 4-point Likert scale with responses including never, sometimes, often or routinely. The four subscales used for this study include health responsibility, exercise, nutrition, and stress management. Alpha coefficients have ranged from 0.78 to 0.93 for the subscales [67].

Accelerometry will be measured for 7 continuous days using the Computer Sciences and Applications (CSA) uniaxial accelerometer to capture weekday and weekend physical activity. Accelerometers do not rely on self-report and provide an objective measure of physical activity [68,69]. Information from the use of accelerometry assesses the intensity, frequency, and duration of activity performed [68]. Taking multiple days of CSA measurements and averaging them has been reported to increase alpha coefficients from 0.42-0.47 for 1 day to 0.7 for 4 days in adults [69,70]. The research assistant will explain the accelerometer to the mother and review the procedure. The mother will be provided with a log book to keep track of her daily activity and a phone number to call if she needs help. Mothers will be provided with a mailer to mail the accelerometer back at the end of the 7 days. A research assistant will send out a text message to the mother in the morning to remind her to put her accelerometer on.

### Self-efficacy outcomes

The Eating Self-Efficacy Scale [71] will be used to measure dietary self-efficacy. The questionnaire consists of 25-tems and will ask women to rate their difficulty in controlling eating on two subscales, which include the negative affect scale and the socially acceptable scale with a 1 reflecting no difficulty to a 7 reflecting a high degree of difficulty. Socially acceptable eating is defined as overeating at holiday or family events. Negative affect eating is defined as emotional eating. Alpha coefficients have been found to be 0.85 for the socially acceptable eating subscale and 0.94 for the negative affect subscale [71].

Breastfeeding Self-Efficacy will be measured using the Breast Feeding Self-Efficacy Scale [72]. The 14-item questionnaire will ask women how sure they are regarding breastfeeding with a 1 reflecting not at all confident to a 5 reflecting very confident. Alpha coefficients range from .92 to .96 [72].

### Infant outcomes

For infant feeding and growth (Aim 3), we will measure breastfeeding duration and intensity as a modifiable risk factor for maternal and infant metabolic disease. We will define breastfeeding duration as the time since birth, in weeks, until the mother stops breastfeeding or expressing milk for her infant. We will define exclusive breastfeeding as the time, in weeks, until the mother introduces formula or complementary foods. We will define breastfeeding intensity as the percent of all milk feeds that are breast milk (# of breast milk feeds per day) / (# of breast milk + formula + other milk feeds per day) [73,74]. We will measure weight-for-length in infants, using standardized weight-for-length z scores [75]. Length will be measured twice and averaged using a portable length board and weight will be measured twice and averaged using a portable calibrated digital scale according to procedures.

### Demographic data

Women will complete a demographic form, including questions about age, race/ethnicity, marital status, and income level.

### Procedures

The project manager will call women who have shown an interest in the study, give a verbal description of the study and ask pre-pregnancy height and weight. If they meet inclusion criteria, the research assistant will schedule an appointment and meet the woman at the site. The research assistant will give the woman an oral description of the study, requirements of participants, and the risks and benefits of participating; random assignment will be explained; and all questions will be answered. After informed consent, physiological data will be collected in a private room at the site. The research assistant will collect data in the same order each time: height, weight, waist circumference, triceps and subscapular skinfolds, and questionnaires, which should take 45 minutes. The 3-hr OGTT at Time 1 will be abstracted from the medical record. Data on infant length-by-weight will be collected following standard procedures.

### Data management

Participants will be tracked using ID numbers. All data will be double entered by different research assistants into a SAS database and backed up on a secure central computer network system. Comparisons will be run for the two versions, and inconsistencies will be checked against the raw data and corrected. Data will undergo range, consistency, and outlier checks. An audit trail will be established to document any changes.

### Data analysis

#### Aim 1

To determine the acceptability of the intervention sessions and materials, the investigators will analyze the interventionists’ field notes and exit interviews with women, which will be tape-recorded with participants’ permission, transcribed, and analyzed for themes. The findings will be used to further adapt and refine the intervention*.* To assess other aspects of feasibility, recruitment yield will be described by the number contacted and the number screened required to yield one enrollment. Interventionists will keep attendance records for each class. Retention will be described at each time point. Statistics on data collection, such as duration of collection per woman, will also be computed at each time point. Rates of recruited, screened, and retained women will be presented by group and time point, along with 95% confidence intervals; the upper bounds will provide an estimate of worst case values for rates in a future study.

#### Aims 2 and 3

To analyze maternal outcomes, descriptive statistics will be calculated for each measure at each time point. All analyses will be conducted using an intention-to-treat approach. Standardized effect sizes for each measure will be calculated for each time point as the ratio of the mean difference between the intervention and wait-list control group to its standard deviation. Correlation matrices will be computed to describe the degree of correlation of each measure across the repeated measures for each group. For the assessment of trends in Aim 2, preliminary analyses will be conducted to determine whether, despite randomization, the intervention and control groups were unbalanced at baseline on any measured variable. Any such variable will be examined for statistically significant relationships with any of the outcome measures, and if any are found, the variable will be considered as a covariate for subsequent models.

For each outcome mentioned in **Aims 2 and 3**, a separate linear mixed-effects model will be constructed. These will model data across all available post-baseline time points; contrasts will be constructed to evaluate the effects of the intervention over the post-baseline period, as compared to the wait-list control group, with covariate adjustment for baseline values. These models will include assessment for main effects for experimental group, time point, and site, as well as interactions, and will account for the within-site and within-subject correlation structure invoked via the study design. This approach will provide useful information in guiding the analysis of a future study. Least-squares means will be computed and plotted for each time point for each group to determine average trajectories for each measure.

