## Methods

### Design

The study will use a two-group, randomized, repeated measures design to test the feasibility of the adapted NEST intervention for women diagnosed with GDM during their current pregnancy. See Figure 1. An experimental group of women (n = 50) will receive a two-phased intervention with follow-up. In Phase I (Intensive Intervention), interventionists will meet with women in small groups for 14 sessions. The initial session, during pregnancy, will focus on the benefits of and strategies to sustain breastfeeding. The remaining sessions, on diabetes, nutrition and exercise education, coping skills training, exercise, and a home-based exercise program, will start when they are about 6 weeks postpartum. Participants will also receive weekly educational and motivational text messages. In Phase II (Continued Support), interventionists will hold monthly meetings with the women for 3 months to discuss problems related to breastfeeding, nutrition and exercise, and to provide feedback and support. Data will be collected at baseline at 22–36 weeks pregnant (Time 1), to 6 weeks postpartum (Time 2), 4 months postpartum and completion of Phase I (Time 3), 7 months postpartum and completion of Phase II (Time 4), and 10 months postpartum, after 3 months on their own (Time 5). Time 3 and Time 4 data collections will determine the magnitude of intervention effects after Phase I and Phase II respectively; Time 5 will determine whether women have maintained their new skills. Three to 6 months after completion is a standard length of time for follow-up in weight management studies [52].

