### Power analysis

Eighty women are expected to complete the study; 40 per group. We will induct 100 women to take into account a 20% attrition rate seen in our previous studies [37-39,53]. While individually randomizing women to either the experimental or wait-list control group would be ideal, this is not feasible in our settings because of the limited number of women with GDM available in each site during any given enrollment period. Therefore, we have chosen a cluster-randomized approach. After a group of women is inducted, they will be randomly assigned to either the experimental group or the wait-list control group, to provide a balanced allocation in each site, yielding a random sequence of two experimental groups and two wait-list control groups for each site. This will provide two-group, longitudinal comparisons of complete data on 40 women per group, for analyses of changes in metabolic, clinical, weight, adiposity, health behaviors, and self-efficacy at up to four post-baseline time points. A cluster power calculation was performed with POWERLIB20 SAS/IML modules, which incorporate the methods described in Muller [54]. These methods calculate power for the general linear multivariate model, including repeated measures data, allowing adjustment for within-cluster correlation, which is expected to be small. We intend to determine effect size for each maternal and infant outcome addressed in Aims 2 and 3 in separate multivariate models. The study will be well powered to detect moderate to large effect sizes. An effect size of .67 SD at any post-baseline time point with this sample size will provide .80 power at the two-sided .05 significance level; an effect size of .8 SD increases the power to .92.

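### Aim 1 takes the upper 95% confidence bounds of recruitment and retention rates as the worst case for a future study; for these rates the lower bound is the worst case

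*Protocol article*

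**What the plan says.** Under Aim 1 in the Data analysis section, the protocol article describes several feasibility summaries in one paragraph:

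- Recruitment yield is an inverse measure: "recruitment yield will be described by the number contacted and the number screened required to yield one enrollment".
- Follow-up is expressed as retention, not loss: "Retention will be described at each time point".
- Interval estimates are then announced: "Rates of recruited, screened, and retained women will be presented by group and time point, along with 95% confidence intervals".
- The same sentence gives the rule for using those intervals: "the upper bounds will provide an estimate of worst case values for rates in a future study".

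The Power analysis section supplies the planning values: "Eighty women are expected to complete the study; 40 per group", and "We will induct 100 women to take into account a 20% attrition rate seen in our previous studies".

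**The concern.** A confidence bound is a worst case only if it lies on the unfavourable side of the estimate. A future study is harder to run if fewer women enroll or fewer stay, so the pessimistic limit for a recruitment or retention rate is the lower one. The sentence names rates of women recruited and retained and points to the upper limit. It therefore labels the most optimistic plausible value as the most pessimistic.

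Feasibility is the first aim, recruitment and retention are among its listed components, and the Discussion says the trial is meant to lay the ground for an efficacy study. This sentence is the only one under Aim 1 that says how the interval estimates are to be carried forward. A planner who takes it at face value would start from a retention figure that is too high.

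**Working it through.** **Inputs, all from the Power analysis section:** 80 expected completers, 20% attrition, 100 women enrolled.

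**Step 1. Reproduce the plan's own figure.** Enrollment = completers / (1 − attrition) = 80 / (1 − 0.20) = 100. This matches the plan exactly, so expected retention is 80/100 = 80%.

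**Step 2. Exact (Clopper-Pearson) 95% interval for x = 80 retained of n = 100.**

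- Lower limit: the 2.5% quantile of Beta(x, n − x + 1) = Beta(80, 21), which is 0.708.
- Upper limit: the 97.5% quantile of Beta(x + 1, n − x) = Beta(81, 20), which is 0.873.

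Retention is therefore 70.8% to 87.3%. In terms of attrition (1 − retention), it is 12.7% to 29.2%.

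**Step 3. Turn each limit into an enrollment.** The documents state no target for a future study, so this trial's 80 completers serve as an illustration. Enrollment = 80 / retention, rounded up.

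| Retention used | Value | Enrollment for 80 completers |
|---|---|---|
| Upper bound (the rule as written) | 87.3% | 80 / 0.873 → 92 |
| Point estimate | 80.0% | 80 / 0.800 = 100 |
| Lower bound | 70.8% | 80 / 0.708 → 113 |

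The supposed worst case needs fewer women than the point estimate, which a pessimistic value cannot do. If 92 were enrolled and retention were 70.8%, about 92 × 0.708 = 65 women would complete.

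**Step 4. Sensitivity to the interval method.** Wilson limits for 80/100 are 71.1% and 86.7%, giving 113 and 93. The conclusion does not depend on the method.

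**Step 5. Direction for recruitment.** The documents give no number screened, so one is assumed. With 100 enrolled of 200 screened, the exact interval for the enrollment rate is 42.9% to 57.1%. Screens per enrollment are 1/0.429 = 2.33 at the lower bound and 1/0.571 = 1.75 at the upper. Across assumed totals of 150 to 400 screened, the lower bound always requires more screening: 1.71 against 1.35 per enrollment at 150, and 4.80 against 3.38 at 400.

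**The case against.** The strongest reply is that this is a slip of wording. Two other quantities in the article do have their worst case at the upper bound: the number contacted or screened per enrollment, in the same paragraph, and the attrition rate used to size the trial. The authors may have had these in mind. That may explain the sentence but does not rescue it. The sentence names recruited and retained women, the paragraph speaks of retention, and nothing in the article recasts these as loss or refusal rates.

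A second reply is that the consequence is limited, and this stands. The full intervals will be presented, so the lower limits remain visible. The article contains no sizing formula or progression criterion that depends on the label.

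Several stronger readings are tempting, but the documents do not support them:

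- A reader might infer that the next trial would necessarily be too small. The plan states no rule that converts the bound into a sample size; 92 against 113 is an illustration.
- A reader might extend the reversal to the screening rate. No denominator is given for it, so its favourable direction is undefined.
- A reader might infer that screening and recruitment rates cannot be shown by group because they precede allocation. Whole cohorts are allocated, so each cohort's logs can be tabulated afterwards under the arm it received.
- A reader might apply the interval for one arm (40 of 50 retained) to the total of 80 completers and get a wider contrast. That treats both arms as sitting at their own limit together; the matching calculation uses 80/100.
- A reader might fault the absence of intervals adjusted for clustering. That detail may properly sit in the full protocol or analysis plan, which is not at hand.

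**Conclusion.** The point holds for recruitment and retention rates: the bound named as the worst case is the best case. At the expected retention of 80/100, the rule would carry forward 87.3% where the pessimistic value is 70.8%, or 92 enrolled against 113 for 80 completers.

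The size rests on three assumptions: retention turns out as planned, women are treated as independent, and 80 completers is the illustrative target. Correlation within cohorts would widen the interval without changing the direction.

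This is a minor-to-moderate correction to the feasibility output. A reader might infer that it weakens this trial's own results. It does not, because the enrollment of 100, the power statement and the analyses for Aims 2 and 3 make no use of this rule.

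**What to change.** Replace the closing clause of the Aim 1 analysis paragraph with wording such as: the lower 95% bounds for recruitment and retention rates (equivalently, the upper bounds for attrition and for the number contacted or screened per enrollment) will provide the worst-case values for a future study.

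The cost is one sentence. Data collection, trial procedures and the other analyses are unchanged.

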### Sample

The trial received ethical approval by the Institutional Review Board at The University of North Carolina at Chapel Hill, REX Healthcare and WakeMed. Women between 22–36 weeks of pregnancy who are diagnosed with GDM are eligible to enroll in the study. Inclusion criteria include a diagnosis of GDM during the current pregnancy by two or more 100 g Oral Glucose Tolerance Test values exceeding established thresholds (fasting 95, 1 h 180, 2 h 155, 3 h 140 mg/dL) [55]; age 18 years or older; a pre-pregnancy body mass index ≥ 25 kg/m^2^; ability to read and write in English; and willingness to consent for themselves and their infant. Health care providers will not be asked to give permission for women to join the study. Women will be excluded if they have an A1C ≥ 6.5 mg/dL indicating T2DM. The project manager contacted both sites and met with health care providers and staff to explain the study and distribute brochures. Any woman diagnosed with GDM who meets the inclusion criteria is given a brochure and asked to call the study number. The woman is then screened over the phone by the project manager. If the woman meets inclusion criteria and is interested in joining the study, an enrollment appointment is set up at one of the community centers at a convenient time for the woman to confirm eligibility and review the consent. The project manager confirms eligibility, explains the study, and answers all questions before asking the woman to consent for herself and her infant.

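### The Aim 2 models pick extra covariates by baseline imbalance and then association with any outcome; a fixed set, with pre-pregnancy BMI and gestational age for weight, would be better

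*Protocol article*

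**What the plan says.** The protocol article, Data analysis, Aims 2 and 3, sets out the rule for the Aim 2 trend analyses in three steps.

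1. Imbalance: "preliminary analyses will be conducted to determine whether, despite randomization, the intervention and control groups were unbalanced at baseline on any measured variable". No criterion for imbalance is given.
2. Association: "Any such variable will be examined for statistically significant relationships with any of the outcome measures".
3. Consequence: "if any are found, the variable will be considered as a covariate for subsequent models".

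The same section fixes part of the model for every outcome. Contrasts are estimated "with covariate adjustment for baseline values", and the models assess "main effects for experimental group, time point, and site, as well as interactions".

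Four other places bear on the point:

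- Aims makes weight, with fasting glucose, a primary maternal outcome, assessed from Time 1 to 10 months postpartum. Time 1 is a visit at 22 to 36 weeks of pregnancy.
- Sample requires "a pre-pregnancy body mass index ≥ 25 kg/m^2" and a gestational age of 22 to 36 weeks.
- Procedures has the project manager telephone interested women, "give a verbal description of the study and ask pre-pregnancy height and weight".
- Table 2 shows that waist circumference is not measured during pregnancy, so it has no Time 1 value.

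**The concern.** This is a stated selection rule, so it is not a detail left to the analysis plan. It has three weaknesses.

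- The second step uses outcome data, so the covariates cannot be known until the outcomes have been looked at.
- Association with any outcome is enough. A variable linked to, say, blood pressure could be carried into the weight model.
- Inclusion is only considered, so the decision is open after the data are seen.

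The rule also asks the wrong question. A covariate earns its place by predicting the outcome, whether or not the groups happen to differ on it. A strongly prognostic variable that is balanced never reaches the second step, and its precision is lost.

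Weight shows this most clearly. Its fixed baseline covariate is a pregnant weight taken anywhere in a 14-week window, so it mixes a woman's usual weight with her stage of pregnancy. Two variables that would help separate them, pre-pregnancy BMI and gestational age at Time 1, enter only if the rule happens to select them. For waist circumference, the fixed adjustment for a baseline value cannot be carried out at all.

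**Working it through.** **The plan's own figures.** Power analysis gives 0.80 at 0.67 SD and 0.92 at 0.8 SD, with 40 completers per group and two-sided 0.05. A two-sample t test (78 df, no clustering) gives 0.841 and 0.942. The protocol says it allowed for a small within-cluster correlation but gives no value. There are 2 sites × 4 enrollment groups = 8 clusters, so 80/8 = 10 completers each. An assumed correlation of 0.012 gives a design effect of 1 + 9 × 0.012 = 1.108 and power of 0.803 and 0.919. The stated figures are reproducible on that assumption. They do not settle the covariate question.

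**What the rule does.** Simulation with 40 independent women per group, five candidate covariates and 8,000 runs per scenario. Two candidates are prognostic and together explain a share R² of outcome variance. Both screens are at 0.05; for the imbalance step that level is an assumption, as is R². The effect is 0.67 SD.

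| R² | Power: no extra covariates | Power: plan's rule | Power: two pre-specified | Type I error: rule | Type I error: pre-specified |
|---|---|---|---|---|---|
| 0.10 | 0.836 | 0.833 | 0.866 | 0.050 | 0.053 |
| 0.30 | 0.847 | 0.855 | 0.943 | 0.040 | 0.051 |
| 0.50 | 0.845 | 0.864 | 0.987 | 0.033 | 0.049 |

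The Monte Carlo standard error near 5% is √(0.05 × 0.95/8000) = 0.0024. A second simulation, with 30 candidates in 8 cohorts of 10, gave null rejection of 5.1% and 3.9% for the rule. Across both, the range is 3.3% to 5.1%.

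Share of the available power gain that the rule recovers:

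- R² = 0.10: none (0.833 against 0.836 without covariates).
- R² = 0.30: (0.855 − 0.847)/(0.943 − 0.847) = 0.08.
- R² = 0.50: (0.864 − 0.845)/(0.987 − 0.845) = 0.13.

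The SD of the estimate improves somewhat more. At R² = 0.10 it is 0.2245 with no extra covariates, 0.2220 under the rule and 0.2158 pre-specified, so the rule recovers 0.0025/0.0087, or 29%, of the reduction. The power gain is smaller because the rule's tests are conservative.

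**Size for weight.** The gain is only what the new covariates add beyond Time 1 weight. Assume gestational gain of 0.4 kg per week (SD 0.2). Two women alike before pregnancy but seen at 22 and 36 weeks would then differ by 14 × 0.4 = 5.6 kg at baseline. Under two assumed variance models, adding gestational age and pre-pregnancy weight cuts residual variance from 28.4 to 25.5 (10%) or from 52.3 to 49.3 (6%).

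To express this as power, take an effect of 0.5 SD, 40 per group, a baseline correlation of 0.5 (assumed; residual variance 1 − 0.25 = 0.75) and no clustering. The noncentrality is 0.5/√(residual variance × 2/40).

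| Cut in residual variance | Residual variance | Noncentrality | Power (t test) |
|---|---|---|---|
| none | 0.750 | 2.58 | 0.722 |
| 6% | 0.705 | 2.66 | 0.748 |
| 10% | 0.675 | 2.72 | 0.766 |

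The gain is 2.6 to 4.4 points, in line with the R² = 0.10 row above (0.866 − 0.833 = 3.3 points).

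**The case against.** The strongest defence is that the core of the model is already fixed. Every model adjusts for the baseline value and site; the rule governs only additional covariates, is worded for Aim 2, and says they will be considered. The trial is also presented as a feasibility study to guide a later one. And if gestational age is recorded and differs between groups, the rule could pick it up. All of this stands, and it limits the point to lost precision and an open model.

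Several stronger readings are tempting but not supported.

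- *The rule invalidates the p-values.* Simulated type I error was nominal to conservative. If discretion were used to report the more favourable of two models, a simulation put the error at 5.5% to 6.7%, but nothing in the document says the choice would be made that way.
- *Imbalance will be judged by significance tests and will flag variables often.* Only the association step mentions significance. With no criterion and no count of independent variables, no flagging rate can be derived.
- *The loss is around ten points of power.* The larger gaps in the simulation need covariates that explain 30% or more of the variance beyond the baseline value. Pre-pregnancy BMI probably overlaps heavily with Time 1 weight, so the 6% to 10% range is the relevant one.
- *Glucose models also need gestational age.* No figure in the document supports this.

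It is also fair to say that an article need not list every covariate. The point does not rest on a missing list: it rests on a written rule for choosing covariates and on a baseline adjustment that waist circumference cannot have. Gestational age is not named in Table 2 or under Demographic data; that it is known follows from the entry criterion.

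**Conclusion.** The point holds as a matter of precision and pre-specification. The rule makes the Aim 2 models depend on observed outcomes, lets one outcome decide the covariates of another, and omits prognostic variables that are balanced. It recovered at most about 13% of the available power gain in the simulations and did not raise the false-positive rate. For weight the loss is modest, about 3 to 4 points of power at 0.5 SD.

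That size rests on an assumed gestational gain, an assumed baseline correlation of 0.5 and independent women; the document gives no prognostic strengths. The simulated rule screens against a single outcome, so it does not capture the any-outcome trigger or the discretion over inclusion. Those two defects follow from the wording alone. The change is worth making because it is cheap and the trial expects only 80 completers.

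**What to change.** In Data analysis, Aims 2 and 3:

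- Delete the imbalance-and-association screen. Describe baseline balance by group, without using it to choose covariates.
- Keep the outcome's baseline value and site, as already stated.
- For weight and BMI, add in advance pre-pregnancy BMI and gestational age at the Time 1 visit. List gestational age as a recorded variable in Table 2.
- For waist circumference, name pre-pregnancy BMI as the baseline covariate, since no Time 1 value exists.

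The cost is a few sentences of wording and one or two extra parameters per model. No new measurement is needed beyond writing down gestational age, which eligibility already requires. The drawback is that pre-pregnancy height and weight are self-reported by telephone, so some of the possible gain will be lost to reporting error.
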